#### Photodynamic therapy

2.12.2

Group 2 participants will receive PDT; the technique associates a photosensitive agent with a source of light and oxygen, in order to reduce the microbial load in places that are not accessible by curette.

After scaling, the procedures will be performed as described:

Application of methylene blue (0.005% - Chimiolux 5, DMC - purified water and methylene blue) with a carpule syringe and needle (with stop and without bevel) into the pseudopockets;Wait 1 minute (pre-irradiation time)^[35]^Irradiation with a red laser diode (λ = 660 nm) with an output power of 100mW (Therapy EC, DMC, São Paulo, SP, Brazil). The laser head will be positioned in direct contact with the pseudo periodontal pocket.^[36]^Apply at 8 sites where there is hyperplasia.Wash in abundance with saline solution until the photosensitizer is completely removed.During laser application both patient and operator will wear safety goggles.

Participants in G1 (Control- PDT placebo) will receive an agent with the same vehicle as that of the methylene blue to mimic irrigation with the photosensitizer; the laser will be switched off at the time of application.

PDT placebo procedures will be performed after scaling. The main difference between G1 and G2 is that in G1 the lase will be turned off but the same device will be positioned in the same way and with the same time of G2. Also, the beep sound will be recorded and turned on during application.

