### Study blinding

2.6

Only the researcher responsible for conducting the treatments (who will open the randomized envelopes) will know which treatment is assigned to each patient. The identification of each group will only be revealed by this researcher after statistical analysis of the data for all those involved in the study. Therefore, the researcher responsible for data collection, the microbiologist and the statistician will be blind regarding the treatments assigned to the groups. The patient will also be blind to the type of treatment performed, since the periodontal treatment will be identical in both groups and treatment with PDT will be simulated in the control group.

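### The sham as described does not ensure patient blinding: the placebo irrigant is defined only by its vehicle, and nothing matches or conceals the blue dye

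*Protocol article*

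**What the plan says.** Section 2.12.2 of the protocol article gives the active irrigation step as "Application of methylene blue (0.005% - Chimiolux 5, DMC - purified water and methylene blue", delivered by syringe and needle into the pseudopockets. After a waiting time the laser is applied at 8 sites, and saline is then used to wash the photosensitizer out. The same list says: "During laser application both patient and operator will wear safety goggles".

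For the control arm (G1), participants "will receive an agent with the same vehicle as that of the methylene blue", the purpose being to imitate the irrigation step. The text continues: "The main difference between G1 and G2 is that in G1 the lase will be turned off", with the same device held in the same position for the same time, and "the beep sound will be recorded and turned on during application".

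Section 2.6, Study blinding, states: "The patient will also be blind to the type of treatment performed". It gives two grounds: scaling is the same in both arms, and PDT is simulated in the control arm. The same section says that the researcher collecting data, the microbiologist and the statistician are also blind.

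**The concern.** Patient blinding rests on the simulation, so the simulation has to reproduce what a patient could notice. Colour is an obvious feature of a dye-based treatment, and it is the one feature the sham description does not cover. If G2 patients see blue liquid in the mouth or in the rinse and G1 patients see clear liquid, some patients may work out their allocation.

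Three things are then exposed:

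- **OHIP-14**, completed by the patient at baseline and at 21 days, is directly open to expectation.
- **Plaque index and GI** depend on home care over the 21 days. The Discussion itself ties plaque and bleeding to oral hygiene guidance. A patient who believes the active treatment was given, or withheld, might brush differently.
- **Examiner blinding** could be weakened if a patient mentions the arm. Section 2.7 has one calibrated researcher collect both the baseline periodontal examination and OHIP-14. If that researcher also sees patients at follow-up, the opportunity is there.

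The article gives weight to blinding. The Introduction presents the placebo group as the means of making the study blind, and the Discussion relies on double-blinding to prevent interference with the results.

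**Working it through.** No formula applies, and the plan gives no figure to reproduce. The check sets the descriptions of the two arms side by side.

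| Feature | G2 (PDT) | G1 (placebo PDT) | Matched in the text? |
|---|---|---|---|
| Scaling and hygiene guidance | Given | Given | Yes |
| Irrigant | Purified water plus methylene blue, 0.005% | An agent sharing the vehicle | Vehicle only; colour not addressed |
| Device and position | In contact with the pseudopocket | Same | Yes |
| Application time | As set for PDT | Same | Yes |
| Light | Laser on | Laser off | No, by design |
| Sound | Device in operation | Recorded beep played | Yes |
| Goggles | During laser application | Not repeated for the placebo procedure | Not stated for irrigation or wash-out in either arm |
| Saline wash | Until the photosensitizer is gone | Not mentioned | Not stated |

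1. **Composition.** The active product is given two components. Removing the methylene blue leaves purified water, so on the plain reading the placebo is an uncoloured liquid. The Introduction itself refers to the photosensitizer as a dye.
2. **Concealment.** Goggles are tied to the laser step. Nothing says that they block the patient's view, or that they are worn when the irrigant goes in or is washed out. Those are the two moments at which colour would be seen.
3. **Wash-out.** The saline wash appears among the G2 steps. The G1 description does not say whether it is repeated, which is a second possible cue.
4. **Comparison with section 2.6.** Patient blindness is asserted as a consequence of the simulation. Steps 1 to 3 show that the simulation, as described, leaves out a visible feature of the active treatment, so the conclusion does not follow from the stated grounds.
5. **Reach.** Section 2.13 makes GI the primary variable and OHIP-14 a secondary one. GI is recorded with a probe by an examiner who does not treat (sections 2.4 and 2.12.1) and whose blinding is stated separately. Direct exposure is therefore limited to OHIP-14; the routes to plaque index and GI are indirect.

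**The case against.** The strongest reply is that the text does not say what the placebo looks like. An agent sharing a vehicle need not be the bare vehicle, and its stated purpose is to imitate irrigation with the photosensitizer, so an inert colorant in water is not excluded. The article also condenses a fuller protocol that may give the placebo's appearance.

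Nor is it shown that patients could tell. The design is parallel-group with a single treatment session, so each patient meets one irrigant and has nothing to compare it with. The solution is dilute, it goes by needle into pockets inside the mouth, and the wash-out limits residual colour. The document does not say whether patients learn that the active agent is blue. Finally, the primary outcome is recorded by a separately blinded examiner.

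Much of this stands, and it limits the claim. A reader might infer that the placebo is plain water, that patients will recognise their arm, and that the double-blind label is therefore false. The document supports none of these as fact: the placebo's colour is not given, and what patients would see is an inference.

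The reply does not, however, supply a masking step. The article describes the sham down to the recorded beep and defines the irrigant by its vehicle alone. An unstated colorant is possible, but the blinding claim cannot rest on it.

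**Conclusion.** The point holds in a limited form: patient blinding is asserted but not ensured by the sham as described. It rests on the plain reading of the irrigant description and on the absence of any colour match or concealment in an otherwise detailed account. If the placebo is in fact colour-matched, stating so would settle the matter.

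The directly exposed outcome is OHIP-14. Effects on plaque index and on the primary GI are possible only indirectly. The blinding of the data collector, microbiologist and statistician is stated independently and is not itself contradicted.

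The size of any bias cannot be estimated from the document. It may be tempting to express an assumed shift as a share of the 0.40 effect size in section 2.1, but that figure was set for the amount of bacteria in crevicular fluid, not for OHIP-14, plaque index or GI. A ratio of that kind would mix outcomes. The matter should be corrected because the remedy is cheap and the claim is one on which the article relies.

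**What to change.** Adopt one of two forms of concealment and state it in section 2.12.2:

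- **Conceal the irrigant identically in both arms** from irrigation to the end of the wash-out, for example with view-blocking eyewear compatible with the laser safety goggles, and with the same saline wash and suction in G1; or
- **Use an inert, colour-matched placebo** and state its appearance.

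Optionally, ask each patient at T2 which treatment they believe they received, and report the answers by arm.

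If neither form of concealment is used, revise section 2.6, the Abstract and the Discussion to describe the trial as assessor-blinded, and interpret OHIP-14 as open to expectation bias.

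The cost is a minor addition to the chair-side procedure and a change of protocol wording, plus one question at T2 if the optional check is taken up. Sample size and analysis are unaffected.

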**Table 1 T1:**
[figure not shown]
Parameters used for PDT.

### Study variables

2.13

The primary study variable will be

GI as determined using a periodontal probe at baseline (T_0_), 7 (T_1_) and 21 (T_2_) days after treatment.

The secondary variables of the study will be:

Clinical PD at baseline (T_0_), 7 (T_1_) and 21 (T_2_) days after treatment;Visible PI at baseline (T_0_), 7 (T_1_) and 21 (T_2_) days after treatment;GI at baseline (T_0_), 7 (T_1_) and 21 (T_2_) days after treatment.Oral health-related quality of life (OHRQoL) will be assessed using the OHIP-14 questionnaire at baseline (T_0_) and 21 (T_2_) days after treatment;Evaluation of cytokines IL-6, IL-1β, IL-8, TNF-α and IL-10, by ELISA method, in non-stimulated saliva and crevicular fluid at baseline (T_0_), 7 (T_1_) and 21 (T_2_) days after treatment;Microbiological analysis by means of the *Universal bacteria* count (16S rRNA gene) present in crevicular fluid (sites with hyperplasia), and non-stimulated saliva at baseline (T_0_), 7 (T_1_) and 21 (T_2_) days after treatment.

### Variables

2.14

#### Clinical probing depth

2.14.1

It will be performed by a calibrated evaluator using a periodontal probe marked in millimeters (North Carolina University periodontal probe, UNC-15 (Hu-Friedy^TM^): all teeth (except third molars) will be evaluated at 6 sites (mesiobuccal, buccal, distobuccal, mesiolingual, lingual, distolingual) using the aforementioned parameters.

The North Carolina University periodontal probe will be insert in the gingival sulcus. Probing depths to be evaluated in millimeters (mm) from the base of the periodontal pocket to the free gingival margin.

#### Visible plaque index

2.14.2

It will be visualy evaluated before of probing depht, using the following score of visible supragingival plaque: Presence = 1; Absence = 0

#### Gingival index

2.14.3

It will be evaluated by recording the presence or absence of bleending up to 30 seconds after the determination of probing depht. The number of positive sites bleeding will be record and than expressed as percentage of the number of sites examined. Using the following score of bleeding when probing gingival margin: Presence = 1; Absence = 0

#### Analysis of oral health-related quality of life - OHIP-14

2.14.4

The OHIP-14 questionnaire is a simplified form of the original OHIP-49 questionnaire and will be used to assess the impact of oral health on the quality of life of the research participants. The OHIP-14 is used to measure perceived needs; evaluating the impact of oral changes on Oral health-related quality of life. The patient responds to 14 questions by assigning the values:

0 (never),1 (almost never),(sometimes),(most of the time),(always) to his or her answers.

In this study it will be evaluated the OHIP-14 using the additive method and domain evaluation. In the additive method, when the value is greater than 1, one can consider the presence of a negative impact on the life of the individual. OHIP-14 will be assessed at baseline and after 3 weeks for all subjects.

#### Microbiological analysis

2.14.5

##### Biofilm collection

2.14.5.1

Biofilm samples from regions with gingivitis and gingival hyperplasia (pseudo pocket) will be collected from the supragingival portion to avoid contamination of the sample. The site is isolated with cotton rolls. The paper cone is inserted until resistance is felt. The cone will remain in this position for 30 seconds. If there is blood contamination a new cone will be used after 90 seconds. Five cones must be collected, one for each cytokine. The cones will be placed in a 1.5 ml microcentrifuge tube (Eppendorf) and stored at -80°C. During collection they will be properly identified and stored on ice inside a Styrofoam container. The collected samples will be stored at -80°C until further analysis is performed.

##### Saliva collection

2.14.5.2

Samples of unstimulated saliva (5 ml) will be collected in 50 ml tubes (Falcon tube). In the laboratory 500 μl of saliva will be added to 500 μl TE, and stored at −80° C.

##### DNA extraction

2.14.5.3

DNA extraction will be performed using Meta-G-Nome DNA Isolation - MGN0910 (Epicenter Technologies Corp. Chicago, IL, USA) according to the manufacturer's instructions. For saliva and biofilm samples, 100 μl of sample, previously vortexed at 12857 g (10,000 RPM), 4° C, for 10 minutes, will be transferred to new micro centrifuge tubes. The supernatant will be discarded, leaving 25 μl, along with the precipitate. Samples will be vortexed for resuspension of the pellet. For each sample a mixture of 2 μl of proteinase K and 300 μl of TCL (tissue and cells lysis) will be added; the samples will then be placed in a water bath for 15 minutes and vortexed every 5 minutes. After the water bath, the samples will be placed on ice for 5 minutes. 150 μl of protein precipitation reagent will be added and the samples will be vortexed for 5 seconds. They will then be centrifuged for 10 minutes, at 4°C, at 10,000 RPM. The supernatant will be discarded, leaving only the pellet. 500 μl of isopropanol will be added and the samples will be poured 40 times. Then the samples will be centrifuged again for 10 minutes, at 4°C, at 4,000 RPM, and then decanted to remove the isopropanol and leave only the pellet. 200 μl of 70% ethanol will be added and the samples will be centrifuged for 2 minutes, at 4°C and 4,000 RPM. The ethanol will be removed and the last step will be repeated. The tubes will be left open, inverted until dry, for about 30 minutes. After drying, the resulting pellet will be diluted in TE. After DNA extraction, the samples will be stored in a freezer at −20° C and quantified through the use of a spectrophotometer (NanoDrop ND1000 - Thermo Fisher Scientific Inc.).

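### The DNA extraction text keeps the protein pellet and discards the liquid that should hold the DNA; followed literally, it would push the 16S bacterial counts low and make them noisier in both arms

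*Protocol article*

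**What the plan says.** Section 2.14.5.3 of the protocol article names a commercial isolation kit, to be used "according to the manufacturer's instructions", and then sets out the steps with volumes and spin settings.

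- Before lysis, the sample is spun down and concentrated: "The supernatant will be discarded, leaving 25 μl, along with the precipitate".
- For lysis, "a mixture of 2 μl of proteinase K and 300 μl of TCL (tissue and cells lysis) will be added", followed by a water bath and ice.
- Then "150 μl of protein precipitation reagent will be added and the samples will be vortexed for 5 seconds".
- The spin comes next: "They will then be centrifuged for 10 minutes, at 4°C, at 10,000 RPM".
- After that spin: "The supernatant will be discarded, leaving only the pellet".
- 500 μl of isopropanol is then added and mixed in, and the tube is spun again and decanted. Two washes with 70% ethanol, drying and dilution in TE follow.

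The product is the template for the 16S qPCR. Section 2.13 lists the bacterial count among the secondary variables, "present in crevicular fluid (sites with hyperplasia), and non-stimulated saliva at baseline" and at 7 and 21 days. Section 2.1 builds the sample size on the difference in the amount of bacteria in crevicular fluid.

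**The concern.** The procedure discards a supernatant twice before isopropanol is added. The first discard comes before lysis, when the DNA is still inside intact cells in the precipitate, and it is sound. The second comes after lysis and protein precipitation. By then the DNA is in solution and the pellet is, by the reagent's own name, protein. Keeping that pellet and discarding the liquid reverses the separation.

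The later steps point the same way. Isopropanol brings DNA out of solution, and the ethanol washes then clean the DNA pellet. Neither step has much to work on if the solution has already gone.

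At stake is the total bacterial count in crevicular fluid and saliva at all three visits. Counts are read against a plasmid standard curve, and the control described in the qPCR section (2.14.5.4) is water in place of template. Neither corrects for DNA lost during extraction, so any such loss passes straight into the reported count.

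**Working it through.** The protocol gives no recovery figure to reproduce, so the check follows the fractions and volumes through section 2.14.5.3.

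**Volume at the protein-precipitation spin**

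| Component | Volume (μl) |
|---|---|
| Liquid kept with the cell precipitate | 25 |
| Proteinase K | 2 |
| TCL lysis solution | 300 |
| Protein precipitation reagent | 150 |
| Total | 25 + 2 + 300 + 150 = 477 |

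The volume of the solid precipitate is ignored.

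**Isopropanol relative to that volume**

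500 / 477 = 1.05 volumes. An amount about equal to the lysate fits precipitation of DNA from the retained liquid. It has no evident purpose on a drained pellet.

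**DNA kept if the step is followed literally**

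The protocol does not say how much liquid stays with the pellet. Assume a residual volume r between 5 and 50 μl, with the dissolved DNA evenly spread through the liquid and none trapped in the pellet. Then the fraction kept is r / 477 and the shift in the count is log10(r / 477).

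| Residual r (μl) | Fraction kept | Fraction lost | Shift (log10) |
|---|---|---|---|
| 5 | 1.0% | 99.0% | −1.98 |
| 10 | 2.1% | 97.9% | −1.68 |
| 25 | 5.2% | 94.8% | −1.28 |
| 50 | 10.5% | 89.5% | −0.98 |

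The loss is therefore about 90% to 99%, or 1 to 2 log10. DNA trapped in the pellet would make it smaller.

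**Added noise**

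The loss depends on how each tube is decanted. If r varied between tubes over the whole assumed range, evenly on the log scale, the width would be log10(50 / 5) = 1.0. The added standard deviation would be 1.0 / √12 = 0.29 log10. If the fraction kept varied only between 5% and 10%, the width would be log10(2) = 0.30 and the standard deviation 0.30 / √12 = 0.09 log10. The noise is thus modest to material, depending on how consistent the decanting is.

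**Direction**

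Both arms and all three visits go through the same extraction. A loss that is proportional and common to all samples cancels from a between-arm difference on the log scale. What remains is the tube-to-tube variation, plus the chance that samples with few bacteria fall towards the lower end of the standard curve, which runs from 10 to 10^8 plasmids.

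**The case against.** The strongest reply is that this is a slip of wording. The section defers to the kit's instructions, and the surrounding text has other phrases that cannot be meant literally: samples are vortexed for ten minutes at a stated centrifugal force, and poured forty times. The isopropanol volume itself suggests that the supernatant was meant to be kept. The laboratory may well do the step correctly, and the spectrophotometer reading after extraction might reveal a poor yield. This stands as a reason not to conclude that samples are being lost. It does not remove the error. The step is explicit, nothing else in the article corrects it, and nothing says which text governs if it and the kit instructions differ.

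A reader might go further and make three inferences that the documents do not support.

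- *That the counts would be unrelated to the true load, so that an effect of photodynamic therapy on bacteria could not be seen.* Under the assumed residual volumes the counts are shifted down and noisier, but they would still follow the true load. Nothing shows that samples would drop off a standard curve spanning seven orders of magnitude.
- *That the step contradicts the kit manual.* The manual is not shown. The inconsistency that can be demonstrated is with the reagent's name and with the steps that follow.
- *That the comparison between arms is biased.* The loss is common to both arms.

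It is also fair to say that the endpoint is secondary. The gingival index is primary, and neither it nor the cytokine and quality-of-life measures use this extract.

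**Conclusion.** The point holds as an error in the written procedure. Section 2.14.5.3 keeps the wrong fraction after protein precipitation, and this follows from the step names, the stated volumes and basic chemistry. Confidence that the text is wrong is high. Whether any sample has been or will be processed that way cannot be judged from the document.

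If it is followed literally, roughly 90% to 99% of the dissolved DNA is lost, a downward shift of 1 to 2 log10. That range rests entirely on the assumed 5 to 50 μl residual and ignores DNA trapped in the pellet. The consequence is a low and noisier 16S count in both arms. This matters because the crevicular-fluid count is the quantity behind the sample size, and extra measurement noise shrinks the standardised difference that 34 participants are meant to detect. In itself it creates no between-arm bias and leaves the primary analysis untouched.

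**What to change.** 1. Check the step in section 2.14.5.3 against the kit instructions and against what the laboratory actually does.
2. Correct the text: after the protein-precipitation spin, transfer the supernatant to a clean tube, discard the protein pellet, and add the isopropanol to the supernatant. The later spin, ethanol washes, drying and dilution can stay as written.
3. If any samples were processed as written, record which ones and flag this before the bacterial counts are interpreted.

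The correction costs one sentence in the laboratory procedure and a check with the laboratory. It needs no extra samples or patients and no reagents beyond those already listed.

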##### Real-time PCR

2.14.5.4

Quantification of the bacteria will be performed using real-time qPCR using the thermal cycler StepOnePlus Real-Time PCR System (Applied Biosystem, Foster City, CA, USA). The products will be detected via fluorescence using the Quantimix Easy SYG Kit (Biotools, Madrid, Spain), following the protocol recommended by the manufacturer. The following primers will be used for the reaction (Table 2):

